### Data collection and monitoring

Patients will fill out questionnaires both before and after surgery. The operation will be performed by the same surgical team, and colonoscopies will be performed by the same senior endoscopic examiner. The study coordinators will be regularly contacted through monthly meetings. Two research fellows will enter the data into a Microsoft Access database every day.

## Discussion

This study aimed to determine which method of anastomosis (single purse string versus double purse string) is better for preventing complications and improving outcomes after laparoscopic TME for rectal cancer.

Anastomotic leakage is the most common complication in laparoscopic TME and is the best measure of the success of rectal reconstruction. Poor blood supply to the anastomosis increases the risk of developing anastomotic leakage [25]. In patients receiving single purse-string anastomosis, the triangle region and the “cat’s ear” on either side of the anastomosis have poor blood supply and therefore are particularly vulnerable sites [26]. The double purse-string anastomosis eliminates the triangle region and the residual horns, but whether it reduces the risk of anastomotic leakage is not known. In addition, during single-string anastomosis, it is difficult to insert the line stapler to close the rectal stump because of the narrow pelvic space, and multiple applications of the linear stapler may be necessary. The increased number of linear stapler firings increases the risk of developing anastomotic leakage [27].

The incidence of anastomotic bleeding after anterior rectal resection is reported to be 0.4% [28]. The risk factors for anastomotic bleeding have not yet been fully elucidated and so it is difficult to predict or prevent anastomotic bleeding. Whether the double purse-string technique can reduce the risk of secondary bleeding by shortening the length of the anastomosis needs to be explored.

When the anastomosis in low rectal TME is created with the use of a mechanical stapler, the rate of anastomotic stricture is reported to be as high as 20% [29]. Studies suggest that poor epithelial bridging of the exposed serous layer and scar formation may be a reason for the increased incidence of stricture after stapler anastomosis. Anastomotic leakage and anastomotic ischemia are also important causes of anastomotic stricture [29]. A significantly lower incidence of anastomotic complications in one of the groups in this study could indicate that the anastomotic method plays a key role.

Surgical, economic, and oncological outcomes are also important indices of the feasibility and success of an operation. This study seeks to establish whether double purse-string anastomosis has any significant impact on surgical, economic, and oncological outcomes in patients undergoing low anterior rectal resection. Increase in the rate of anal preservation and reduction of defecation and genitourinary dysfunction following laparoscopic low anterior rectal resection will be an indication that the technique could improve the quality of life of patients [30]. Pre- and post-operative assessments of defecation and genitourinary function will allow complete evaluation of the impact of the operation. This randomized controlled trial will also avoid the biases inherent in retrospective evaluations. We expect that the double purse-string group will present fewer anastomotic complications, shorter hospital stays, and reduced medical costs.

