### Study population

The study population will comprise patients with rectal cancer. The inclusion criteria will be (1) low or middle rectal adenocarcinoma, in which the tumor is situated less than 12 cm from the anal verge, (2) diagnosis confirmed by preoperative colonoscopy and biopsy, (3) patient eligible for low anterior rectal resection with laparoscopic TME, and (4) willingness for complete 5-year clinicopathological follow-up. Exclusion criteria will be (1) low rectal adenocarcinoma with anal sphincter involvement, (2) presence of distant metastases, (3) radical resection not performed because of local invasion, (4) presence of other synchronous malignancy or serious disease, and (5) surgery performed as an emergency procedure.

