### Primary and secondary endpoints

The primary endpoint will be the incidence of anastomotic complications (i.e., anastomotic leakage, anastomotic narrowing, and anastomotic bleeding). Anastomotic leakage will include clinical and subclinical anastomotic leakage. The diagnosis of clinical anastomotic leakage is based on the clinical manifestations and the extravasation of contrast medium after rectal enema showed on the computed tomography (CT) scan. However, the subclinical anastomotic leakage has only extravasation of contrast medium [16]. Anastomotic narrowing will include both clinically evident narrowing and subclinical narrowing proved by endoscopic examination at 6 months after surgery. On endoscopy, anastomotic stricture will be diagnosed when the diameter of the anastomotic stoma is less than 11 mm [17]. Anastomotic bleeding will be determined as early postoperative anastomotic bleeding or delayed bleeding, and the bleeding of rectum within the first four weeks after rectal anastomosis will be considered as the early postoperative anastomotic bleeding [18].

The secondary endpoints will be the surgical, economic, and oncological outcomes. Indices of surgical outcome will include surgery duration, intraoperative blood loss, anus retention ratio, ileostomy rate, the number of patients with changed method of anastomosis, bowel function recovery time, mean size of tumor, proximal margin status, distal margin status, number of lymph nodes harvested, and postoperative defecation and genitourinary dysfunction. Economic evaluation includes direct and indirect costs, direct costs will include duration of hospital stay and medical costs, and subsequent direct cost-effectiveness analysis will be performed. Indices of oncological outcome will include tumor-node-metastasis (TNM) stage, histology stage, local recurrence, distance metastasis, disease-free survival, and overall survival.

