### Preoperative evaluation

Data will be collected on age, gender, body mass index, American Society of Anesthesiologists (ASA) class, plasma albumin, hemoglobin, previous abdominal or pelvic surgery, tumor size, distance of tumor from anal margin, and tumor pathological differentiation. All patients will be assessed by the Low Anterior Resection Syndrome (LARS) score [19], Fecal Incontinence Quality of Life Scale (FIQL) [20], International Index of Erectile Function (IIEF) [21], International Consultation on Incontinence Questionnaire (ICIQ) [22, 23], and Female Sexual Function Index (FSFI) [24].

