### Power calculation and sample size

We calculated the sample size by using the calculator available at powerandsamplesize.com/Calculators/Compare-2-Proportions/2-Sample-Equality. A comprehensive analysis of a number of studies showed that the incidence of postoperative anastomotic leakage was 8.3% (154/1861) after single purse-string anastomosis of laparoscopic low anterior resection. The retrospective analysis showed that the incidence of leakage was 1.8% (2/108) in the patients with double purse-string anastomosis of laparoscopic low anterior resection in our hospital. The power computation is aimed at detecting a minimum clinically meaningful odds ratio of 0.203 (i.e., a reduction of 79.7% anastomotic leakage in double purse string as compared with single purse string). To detect this difference with α = 0.05 and power of 1 − β = 0.80, 174 per group would be necessary. Given an estimated dropout rate of 20%, the minimum required sample size would be 436 patients. We plan to enroll a total of 500 patients (250 per group).

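### Tumor size, TNM stage and histology stage are classed as outcomes although the anastomosis cannot change them; anus retention probably has little room to differ

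*Protocol article*

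**What the plan says.** All references are to the protocol article.

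- **Primary and secondary endpoints.** Mean tumor size and the anus retention ratio are among the surgical outcome indices. For the oncological ones: "Indices of oncological outcome will include tumor-node-metastasis (TNM) stage, histology stage", followed by recurrence, metastasis and survival.
- **Preoperative evaluation.** Baseline data include "tumor size, distance of tumor from anal margin, and tumor pathological differentiation".
- **Study population.** Inclusion requires "patient eligible for low anterior rectal resection with laparoscopic TME". Exclusion applies to "low rectal adenocarcinoma with anal sphincter involvement".
- **Surgery, and the two anastomosis sections.** The mesorectal dissection and the planned resection limits are the same for everyone. The arms diverge at transection and closure of the distal rectum, and both end in an end-to-end join of sigmoid colon to rectal stump.
- **Statistical analysis.** Continuous variables are compared by t test and categorical ones by chi-squared test, with significance at P ≤0.05. Survival is compared between arms by the log-rank test. Cox regression is planned only to identify independent predictors of prognosis.
- **Discussion.** The trial is to establish whether the double purse-string method has a significant impact on surgical, economic and oncological outcomes. The next sentence treats "Increase in the rate of anal preservation and reduction of defecation and genitourinary dysfunction" as an indication that the technique could improve quality of life.

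**The concern.** An outcome should be something that the randomised treatment can change. Tumor size, stage and histology describe the disease that was removed, and the way the bowel is then joined has no route to affect them. By the article's own definitions they nevertheless belong to the outcomes on which an impact is sought. A chance imbalance in stage could therefore be published as an oncological result of the technique. The same imbalance would also disturb the unadjusted survival comparison, with no planned between-arm analysis that takes it into account.

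Anus retention raises a different question. If nearly every eligible patient keeps the anus in both arms, the rate can hardly rise, and the Discussion would rest a quality-of-life reading on very few events.

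**Working it through.** **The plan's own figure.** The sample size is built on leakage of 8.3% versus 1.8%, two-sided α 0.05 (sidedness is not stated, but two-sided reproduces the result) and 80% power. With unpooled variance:

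n = (0.083 × 0.917 + 0.018 × 0.982) × ((1.960 + 0.842) / 0.065)² = 174.2

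This agrees with "174 per group would be necessary". With 20% dropout, 174 / 0.8 = 217.5, rounded up to 218 per group, or 436 in total. The calculation is sound, but it concerns leakage and says nothing about the items discussed here. What matters below is the planned enrolment of 250 per arm.

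**Can the technique change the three tumor items?**

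| Item | Where it is listed as an outcome | What determines it |
|---|---|---|
| Mean tumor size | Surgical outcome (tumor size is also recorded before surgery) | The disease |
| TNM stage | Oncological outcome | The disease, read from a resection common to both arms |
| Histology stage | Oncological outcome | The disease |

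The expected treatment effect on each is zero, so each test at 0.05 has a 5% chance of a false difference. For three independent tests:

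1 − 0.95³ = 1 − 0.857 = 0.143, about 14%.

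The three items describe the same tumor and are likely to be positively correlated, which lowers this figure. It is an upper illustration, not an estimate.

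**Room for anus retention to differ.** The article gives no expected rate, so the rate p in one arm is an assumption, varied from 90% to 99%. In the most favorable case the other arm reaches 100%. With n = 250 per arm, difference Δ = 1 − p and average rate p̄ = (1 + p) / 2:

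z = [Δ − 1.96 × √(2 p̄ (1 − p̄) / n)] / √(p (1 − p) / n), and power = Φ(z).

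- At p = 98%: z = (0.02 − 1.96 × 0.00890) / 0.00885 = 0.29, power 61%.
- At p = 99%: z = (0.01 − 1.96 × 0.00631) / 0.00629 = −0.38, power 35%.

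| Assumed rate in one arm | Patients not retaining, of 250 | Power if other arm is 100% | Power if half the shortfall is recovered |
|---|---|---|---|
| 90% | 25 | >99% | 57% |
| 95% | 12.5 | 95% | 31% |
| 97% | 7.5 | 79% | 20% |
| 98% | 5 | 61% | 15% |
| 99% | 2.5 | 35% | 10% |

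The normal approximation is rough where so few events are expected, so the lower rows indicate order of size only.

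**The case against.** **The article separates pathology elsewhere.** Study design and Postoperative evaluation both name pathological findings as a category of their own, distinct from complications and survival. That is fair, but the endpoint section is where outcomes are defined, and there the three items are outcomes. Recording size again on the specimen is reasonable and does not make it an outcome of the join.

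**The Discussion never credits stage to the technique.** The quality-of-life sentence names only anal preservation and function, and the functional part is valid, with measures before and after surgery. This stands for that sentence. The sentence before it, however, seeks an impact on surgical and oncological outcomes as a whole, which by definition includes the three items.

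**Stage can already enter the Cox model.** It can, but that model is planned to find predictors of prognosis. The comparison of arms is the unadjusted log-rank test.

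**Anus retention is a legitimate randomised outcome.** This objection largely succeeds. Retention is settled during surgery, after allocation. The article describes technical difficulty in the narrow pelvis with both techniques, and it counts patients whose anastomosis method was changed. The two methods could fail at different rates, and at an assumed 90% to 95% a complete gain would be detectable.

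A reader might infer that retention is practically certain, so that any difference must be chance. The documents do not support that: they give no rate, and eligibility is a preoperative judgement that does not guarantee the result. Nor must every difference in the tumor items be chance. The exclusion for radical resection not being performed because of local invasion can become known only at surgery. If it is applied after allocation by unblinded surgeons, selection could create a difference. That would still not be an effect of the technique.

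**Conclusion.** The point holds for tumor size, TNM stage and histology stage. They are tumor characteristics listed as outcomes, and the planned testing would let a prognostic imbalance pass for an impact of the technique. The risk of at least one false difference is up to about 14%, assuming independent tests at 0.05, and lower with positive correlation.

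For anus retention only a probable ceiling can be claimed. It is inferred from the eligibility criteria and from the sphincter-preserving nature of both arms. If the rate is 98% to 99%, power is 61% to 35% for the largest possible gain; if it is 90% to 95%, that gain would be detectable. To say that this objective cannot be answered would go beyond the documents.

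The primary endpoint and the sample size are not affected.

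**What to change.** 1. Remove mean tumor size, TNM stage and histology stage from the endpoint list. Report them by arm as tumor characteristics, without outcome testing.
2. Alongside the log-rank test, specify a Cox model that compares the arms on disease-free and overall survival with TNM stage as a covariate. Stage is already collected. Although it is read after surgery, the technique cannot alter it, so adjusting for it does not remove any treatment effect.
3. Report anus retention descriptively among all randomised patients, with the reasons for each failure.
4. Soften the Discussion so that the quality-of-life reading rests on the defecation and genitourinary measures, with anal preservation mentioned only as a descriptive result.

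The cost is wording, a shorter list of outcomes and one additional model. No new data are needed for the tumor items; anus retention needs only the reason for each failure to be recorded.

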## Trial status

The study is not yet open for participant recruitment.

## Abbreviations

CT: Computed tomography
FIQL: Fecal Incontinence Quality of Life Scale
FSFI: Female Sexual Function Index
ICIQ: International Consultation on Incontinence Questionnaire
IIEF: International Index of Erectile Function
LARS: Low Anterior Resection Syndrome
SPIRIT: Standard Protocol Items: Recommendations for Interventional Trials
TME: Total mesorectal excision
TNM: Tumor-node-metastasis
